#### Data monitoring

The investigators believe that an independent data safety and monitoring committee (DSMB) is unnecessary given the much less invasive nature and superior safety profile of the experimental treatment arm (thermal ablation). An independent monitor committee (Clinical Research Bureau; CRB) is appointed to safeguard the quality of all investigator-initiated studies. A quality officer from the CRB will monitor all study data according to Good Clinical Practice (GCP). The informed consent of selected individual participants will be checked. Source Data verification will be performed during onsite monitoring (to verify if all data on the Case Report Form are in accordance with the source data). The intensity of this verification is in relation to the risk associated with the intervention investigated, which is considered acceptable. For all subjects, the informed consent forms, the in- and exclusion criteria and the primary outcome (overall survival from the date of randomization to the date of death due to any cause) will be verified. The monitor will also verify if all (S)AE’s are reported adequately and within the time that is determined by legal rules and regulations.

Shortly after beginning of the study the research group and epidemiologists will compose a detailed plan regarding futility and criteria to end the study prematurely. The interim analysis will be performed on the primary endpoint using a non-inferiority analysis. If at interim analysis, after having randomized 30% of the patients, the number of deaths due to treatment is significantly higher in patients included in the experimental arm B compared to patients included in the control arm A, the study will be ended prematurely. If the interim analysis shows a trend towards a type 1 or type 2 error, we will add a Data Safety and Monitoring Board (DSMB) to our study. A new interim analysis will be conducted after having randomized 50% of the patients.

#### (Serious) adverse events (AE’s and SAE’s) and serious adverse device effects (SADE)

All serious adverse events that occur in the first 90-days after the procedure that are life threatening or result in death, both related and unrelated to the research, and serious adverse events that happen during complete study follow up, that are life threatening or result in death and are related (unlikely, possible, probable or definite) to the research according to one of the principal investigator, will be reported within 7 days after the responsible investigator has first knowledge of the adverse reaction. This is for a preliminary report with another 8 days for completion of the report. Relationship of the event to the research will be established by the primary investigator as: 1 = Unrelated (clearly not related to the research), 2 = Unlikely (doubtfully related to the research), 3 = Possible (may be related to the research), 4 = Probable (likely related to the research), 5 = Definite (clearly related to the research). All participating clinicians will be made aware of the necessity to report (serious) adverse events to the principal investigators. The sponsor will report the SA(D)E’s through the web portal *ToetsingOnline.nl* to the accredited EC that approved the protocol, within 15 days after the sponsor has first knowledge of the serious adverse events.

The expedited reporting will occur not later than 7 days after the responsible investigator has first knowledge of the adverse event. This is for a preliminary report with another 8 days for completion of the report.

The sponsor (also) has an insurance which is in accordance with the legal requirements in the Netherlands (Article 7 WMO and the Measure regarding Compulsory Insurance for Clinical Research in Humans of July 1st, 2015). This insurance provides cover for damage to research subjects through injury or death related to study participation.

#### Cost-effectiveness analysis

##### General considerations

For this clinical trial, a cost effectiveness (utility) analysis will be performed from a societal perspective, using a 3-year time horizon. The direct and indirect costs will be included. Direct costs taken into account will include treatment costs, cost of hospitalization, medication, imaging, laboratory testing and pathology.

Within the trial, resource use will be monitored and this will be linked to integral cost prices or Dutch tariffs.

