Additional unablatable CRLM should be resectable	Immunotherapy ≤6 weeks prior to the procedure
Maximum number of CRLM 10	Chemotherapy ≤6 weeks prior to the procedure
Resection for resectable lesions considered possible obtaining negative resection margins (R0) and preserving adequate liver reserve	Pregnant or breast-feeding subjects. Women of childbearing potential must have a negative pregnancy test performed within 7 days of the start of treatment
Resectability and ablatability should be re-confirmed by intra-operative ultrasound (IOUS) and full surgical exploration	Compromised liver function (e.g. signs of portal hypertension, INR > 1,5 without use of anticoagulants, ascites)
Eastern Cooperative Oncology Group status (ECOG) 0–2	Uncontrolled infections (> grade 2 NCI-CTC version 3.0)
American Society of Anesthesiologists (ASA) grade 1–3	Severe allergy to contrast media not controlled with premedication
Life expectancy of at least 12 weeks	Any condition that is unstable or that could jeopardize the safety of the subject and their compliance in the study;
Adequate bone marrow, liver, and renal function as assessed by local usual laboratory tests. As usual, these results should be judged by the local investigator and should be conducted within 7 days prior to definite inclusion. Written informed consent	Substance abuse, medical, psychological or social conditions

The total duration of the study is around 13 years considering an inclusion time of 3 years and a minimum follow-up period of 10 years. All participants will provide written informed consent.The flow diagram of is shown in Fig. 1.

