#### Follow-up

Conferring to national guidelines follow-up will include imaging, laboratory tests including tumour markers (CEA) and clinical examination every 3 months for the first year and every 6 months hereafter. Follow-up cross-sectional imaging should include at least an abdominal ceCT or upper abdominal ceMRI at the given time-points. Participating centres are free to add ^18^F-FDG PET-CTs at specific time-points or to use alternating specific modalities, as long as the follow-up protocol is pre-approved by the trial coordinators and as long as follow-up imaging is identical for both treatment arms. Quality of life questionnaires will be assessed at baseline, every 3 months for the first year and every 6 months hereafter accordingly. Data will be collected in Castor EDC® [33], only available for related research investigators.

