#### Sample size calculation and statistical considerations

We hypothesize (null-hypothesis) that thermal ablation is non-inferior to surgical resection for the selected patient groups in terms of the primary objective (OS). The Cox proportional hazards model (1-sided; non-inferiority or superiority) is used for sample size calculations (Table 3). Given the superior safety profile we consider a hazard ratio (HR) of 1.3 to represent the upper limit of non-inferiority (non-inferiority margin). An HR of 1.3 corresponds to a 56.5% chance of the ablated patients to die first ((P = HR/(1 + HR) = 1.3/(1 + 1.3) = 0.565 (56.5%)). We will have reached 60% of events (death) approximately 6.5 years after having included the last patient (overall probability of event, pE = 0.6). The calculated sample size therefore is 599 (NS). To account for a 10% drop-out ratio (NDO = 69) prior to randomization and a 3% loss to follow-up (NLTFU = 18) after randomization we need to recruit 687 patients (NI). A total number of 618 patients (687–69 (NDO)) will be randomized (NR) into one of two arms: arm A will undergo surgical resection (*n* = 309) and arm B thermal ablation (n = 309) for appointed target lesions.

**Table 3 Tab3:** Sample size calculation

Significance level (α)	0.05
Power (1-β)	0.80
Hazard Ratio (HR), θ (non-inferiority margin)	1.3
Null-Hypothesis Hazard Ratio, θ_0_	1.0
Recruitment time/study accrual (months)	36
Follow-up time (months)	60
Ratio control vs. experimental: m_2_/m_1_	1.0
Total sample size (N_S_)/total number to be randomized (N_R_)	599
Accounting for 3% loss to follow-up after randomization (N_LTFU_)	18
Accounting for 10% drop-out ratio pre-randomization (N_DO_)	69
Initial pre-randomization sample size – number of included patients (N_I_)	687

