In order to qualify for reimbursement the Dutch health care institute (ZiNL) demands the best available evidence. Currently, thermal ablation is only approved for truly unresectable and small CRLM. Outside the setting of the trial ablations of resectable CRLM are off-guideline and hence not reimbursed. The direct and indirect costs of thermal ablation are considerably lower than that of surgery. We expect even lower indirect costs for patients treated within the study, primarily because thermal ablation of resectable CRLM in patients who by definition qualify as suitable for surgery may be associated with an even lower complication-rate.

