### Partial hepatectomy

Until relatively recent, patients with CRLM could only be cured by surgical resection of the lesions. Although no formal upper limit regarding number and size of CRLM has been established, surgical resection is nowadays considered safe and effective for patients with an adequate performance status if radical resection will leave sufficient future functioning liver parenchyma. In addition, one of the three main hepatic veins must be uncompromised and the liver remnant has to comprise a portal vein, hepatic artery and a bile duct. Clear definitions of what is regarded as resectable are lacking and vary dramatically from center to center on the basis of aggressiveness of the surgical team and the perception of the medical oncologist on when to refer patients [37]. To achieve consensus several societies for surgical oncology and hepatobiliary surgery have previously attempted to postulate resectability criteria (Table 2) [38, 39]. The objective of surgical resection for CRLM should be to remove all macroscopically visible tumour tissue with the intent to achieve cure. Histological tumour free margins and hence the confirmation of having radically resected the metastases remains essential.

Surgical resection has a 5-year OS reaching 31–58% [3, 40]. Although the number of serious adverse events of hepatic resection has decreased considerably in the past two decades, the 90-day mortality (4%) and the complication-rate (40%; major plus minor) are still high [41–43]. In 2007 data from 1059 non-cirrhotic patients who underwent major hepatectomy were analysed [43]. The total percentage of complications was 453 (43%), divided as follows: minor complications 26% (grade I 7%; grade II 19%) and major complications 17% (grade IIIa 10%, grade IIIb 2%, grade IVa 4%, grade IVb 1%). Most frequently encountered complications include per-operative major bleeding, bile duct/gallbladder injury, perforation of adjacent structures, intra-abdominal infection, wound infection, liver abscess, haematoma at incision site, pneumothorax, liver failure and death (4%) [41, 42].

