### Partial hepatectomy versus thermal ablation

Numerous studies reported OS rates for surgery and thermal ablation techniques. Comparing RFA alone to surgery alone numerous observational studies reported corrected hazard ratios for OS between RFA and surgery alone; treatment with RFA was associated with an inferior OS (HR = 1.92; 95%CI 1.44–2.56) [22, 23, 25, 27, 58–61]. Comparing RFA plus surgery to surgery alone other studies reported corrected hazard ratios and allowed for pooling between surgery and surgery plus RFA; no significant difference in OS was found (HR = 1.29; 95% CI 0.71–2.327) [14, 18, 61, 62].

For MWA, a 3-year OS of 23% after surgery and 14% after MWA has been reported [54]. Another study showed a 4-year OS of 70% after surgery and 41% after MWA, although no formal statistical comparison with surgery alone was reported [53]. A more recently published study found 5-year OS rates for surgery versus percutaneous ablation as first intervention of 51.9 and 53%, with a median OS of 65.0 (95%CI 47.3 to 82.6) and 62.1 (95%CI 52.2 to 72.1) months, respectively [19].

Another study reported no significant difference in OS for MWA plus surgery versus surgery alone (3-year OS: 50.9% vs 48.8%) [63]. Median OS was 39 months after surgery and 28 months after MWA plus surgery. In multivariate analysis MWA was no prognostic factor for OS.

Several studies revealed that complications were significantly more common after surgery compared to RFA (relative risk [RR] = 0.47; 95%CI 0.28–0.78) [22–29, 59, 64–66]. Two studies reported serious adverse events in 21–28% after surgery vs 13–37% in the surgery + ablation group [18, 24].

Some studies compared RFA to surgery alone regarding local progression-free survival (LPFS) and DFS; RFA was inferior to surgical resection (+/− RFA) [25, 28, 58]. Comparing RFA plus surgery to surgery alone, RFA plus surgery was associated with a poor LPFS [14, 18, 24, 58, 61]. Assessing DFS, no significant difference between RFA + surgery vs surgery alone was found.

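### The only stated cost-utility horizon is 3 years, so the ICER leaves out most of any survival difference, in whichever direction it lies

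*Protocol article*

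**What the plan says.** Under Cost-effectiveness analysis, General considerations, the article fixes the horizon: "a cost effectiveness (utility) analysis will be performed from a societal perspective, using a 3-year time horizon". The Cost analysis subsection makes total QALYs per arm the health outcome. It also sets the discount rates (1.5% for effects and 4% for costs, with 3% for both as an alternative), a bootstrap, and univariate sensitivity analyses on the main cost items. It names no other horizon. The ICER and QALYs are listed among the main secondary endpoints.

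The trial itself runs much longer. The Design section plans the study "considering an inclusion time of 3 years and a minimum follow-up period of 10 years". The sample size section expects 60% deaths about 6.5 years after the last inclusion. Utility data are scheduled without a stated end: "Quality of life questionnaires will be assessed at baseline, every 3 months for the first year and every 6 months hereafter accordingly". The productivity questionnaire (PRODISC) runs every 6 months. No duration is given for it or for resource-use monitoring.

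**The concern.** A cost-utility analysis should run long enough to contain the differences in cost and in health that the treatments may produce. Here the two sides of the ratio accrue at different speeds. The costs that separate the arms at the outset (procedure, hospital stay, early complications, first sick leave) arise within months. The article already expects these to favour ablation: "The direct and indirect costs of thermal ablation are considerably lower than that of surgery". Deaths accrue over many years, which is why the primary endpoint needs long follow-up.

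A horizon of 3 years therefore sets an almost complete early cost difference against a small part of any difference in life-years. The Dissemination policy section ties the trial's evidence to reimbursement. A 3-year ICER standing alone could show a negligible QALY difference even where the trial's own follow-up would show a material one.

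**Working it through.** **Figures in the document.** The article gives no figure for the share of effect inside 3 years, so there is none to reproduce directly. The design values used below do reproduce its sample size: events = 4 × (1.6449 + 0.8416)² / (ln 1.3)² = 359.3, and 359.3 / 0.6 = 599, as stated.

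**Inputs**
- Hazard ratio 1.3, the largest loss still accepted: "we consider a hazard ratio (HR) of 1.3 to represent the upper limit of non-inferiority (non-inferiority margin".
- Resection 5-year survival of 51.9%, from the surgery-versus-percutaneous-ablation comparison under Partial hepatectomy versus thermal ablation, "with a median OS of 65.0 (95%CI 47.3 to 82.6) and 62.1 (95%CI 52.2 to 72.1) months" respectively.
- Range for sensitivity: "Surgical resection has a 5-year OS reaching 31–58" percent.
- Discount rate for effects: 1.5%.
- Assumptions not in the document: exponential survival, a constant hazard ratio from randomization, and (for QALYs only) a utility of 0.8.

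**Formula.** Mean life-years to horizon T: RM = (1 − e^(−λT)) / λ. Resection λ = −ln(0.519)/5 = 0.1312 per year. Ablation λ = 1.3 × 0.1312 = 0.1705.

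| T (years) | Resection | Ablation | Loss | Share of 10-year loss |
|---|---|---|---|---|
| 3 | 2.480 | 2.348 | 0.132 | 17% |
| 5 | 3.667 | 3.364 | 0.303 | 39% |
| 6.5 | 4.374 | 3.929 | 0.445 | 58% |
| 10 | 5.570 | 4.799 | 0.772 | 100% |

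(Losses are computed before rounding.) Against the 5-year loss, 3 years shows 0.132/0.303 = 44%. At 3 years e^(−0.3935) = 67% of resection patients are alive. With utility 0.8 and 1.5% discounting the QALY losses at 3, 5 and 10 years are 0.102, 0.231 and 0.567, so the 3-year share of the 10-year loss is 18%.

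**Sensitivity of the 3-year share of the 10-year loss (undiscounted)**

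| Input varied | Share |
|---|---|
| Resection median 65.0 months | 17% |
| Median 6.0 years (implied by 60% deaths at 6.5 years, with uniform 3-year accrual) | 16% |
| 5-year survival 58% / 31% | 15% / 26% |
| Resection median 39 months (another cited comparison) | 24% |
| Hazard ratio 1.1 to 1.92, median 65.0 months | 16% to 19% |
| Weibull shape 0.8 to 1.5, median 65.0 months | 19% to 12% |

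**Opposite direction.** With a hazard ratio of 0.8 and the same resection survival, ablation gains 0.094 life-years by 3 years and 0.62 by 10, so 15% of the gain is shown. Alternatively, take only the early mortality in the Discussion: 4% at 90 days after resection and under 1% after ablation (entered as 1%), placed at time zero, with equal hazards afterwards. Ablation then gains 0.03 × 2.480 = 0.074 life-years by 3 years and 0.03 × 5.570 = 0.167 by 10. The cut hides more than half of that gain.

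**Timing of recurrence.** The Discussion cites median disease-free survival of 8–12 months after microwave ablation, and progression-free survival of 16.9 months with radiofrequency ablation plus chemotherapy. Under exponential timing the share of events by 36 months is 1 − 0.5^(36/m): 96% at m = 8, 88% at m = 12 and 77% at m = 16.9.

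**The case against.** **A within-trial horizon shorter than survival follow-up is legitimate.** It can be observed for almost every patient and needs little imputation. The reasons for it, and any longer scenario, may stand in the full protocol. This stands as a reason to keep the 3-year analysis, and the lack of a printed rationale is not the point made here. But the article does fix one horizon for a named endpoint and lists sensitivity analyses that leave it unchanged.

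**A reader might infer that the cut favours ablation only.** The documents do not support that. It holds only if ablation carries a net survival loss. The article expects an equal or better oncological outcome, and its own 90-day mortality figures produce a case in which the cut works against ablation.

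**A reader might also infer that recurrence and retreatment costs mostly fall after year 3.** The cited disease-free and progression-free times put roughly 77–96% of such events inside the window, so this does not hold either.

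**The fraction depends on inputs.** That is correct: one sixth applies to the 10-year reference with median survival of about 5 years, and shorter cited medians raise it. The article gives no cost amounts, so the early timing of costs is a qualitative argument.

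**At a true hazard ratio of 1.3 the one-sided 5% test would declare non-inferiority only about 5% of the time,** so a favourable ICER would normally sit beside a failed primary result. This limits the consequence at the margin itself. It does not remove the point for smaller effects: at a hazard ratio of 1.1 the 3-year share is still 16%.

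**Conclusion.** The point holds as a limitation of the planned ICER, not as a bias towards one arm. On the article's own survival figures, 3 years shows about 17% of the 10-year life-year loss at a hazard ratio of 1.3, with a range of roughly 12–26%, and about 44% of the 5-year loss. It would show a similarly small part of a gain at a hazard ratio of 0.8. These figures rest on parametric survival and proportional hazards. If survival is equal in the two arms, the horizon has no such effect. The primary survival conclusion is untouched. What suffers is a main secondary endpoint, whose health side would barely register the difference that the trial is built to assess.

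**What to change.** In General considerations, keep the 3-year analysis and prespecify an additional within-trial cost-utility analysis over the follow-up available at the primary overall survival analysis, and another at 10 years once that follow-up is complete. Use methods suited to censored costs and QALYs. State that resource-use, EQ-5D and PRODISC collection continue past year 3, and that the cost-effectiveness conclusion will not rest on the 3-year result alone. If the full protocol or analysis plan already contains such an analysis, the published text need only say so.

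The intermediate analysis does not replace the 10-year one: under the base assumptions it would show 39% of the 10-year loss at 5 years and 58% at 6.5 years.

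Cost: protocol wording and analysis time, a later full ICER, more censoring and imputation, and continued resource-use capture. The questionnaires are already scheduled with no stated stop. Resource-use capture has no stated duration, so it should be settled before the first patients pass year 3.

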##### Patient outcome analysis

To assess indirect cost, patients will be asked to fill out the Productivity and Disease Questionnaire (PRODISC) every 6 months. To calculate total indirect costs, the friction cost approach will be used.

##### Cost analysis

the primary health outcome measure in this economic evaluation will be the total quality adjusted life years (QALY) per trial arm. QALYS will be calculated by using the utility scores linked to the various health states of the EQ-5D; in essence the length of time a patient spends in a particular health condition is weighed by the corresponding utility. Missing data on costs and utilities will be imputed using multiple imputation. The difference in total costs and total QALYs in both arms will be used to calculate the incremental cost-effectiveness ratio (ICER): the cost per QALY gained (or cost-savings per QALY gained or lost), using the formula: ICER = (Cintervention - Ccontrol)/(QALYintervention - QALYcontrol). Cost and health effect will be discounted using the Dutch discount rates of 1.5% for health effects and 4% for costs. In addition, to allow comparison with international studies, discount rates of 3% for both health effects and costs will be used as well. To assess the impact of uncertainty, a probabilistic sensitivity analysis will be performed using the non-parametric bootstrap with 5000 replications. The results will be presented on cost-effectiveness planes. In addition, ICER acceptability curves will be presented and univariate sensitivity analyses will be performed focusing on uncertainty around most important costs-items.

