#### Primary and secondary objectives

The main objective is to prove non-inferiority of thermal ablation compared to hepatic resection in patients with at least one resectable and ablatable CRLM (≤3 cm) and no extrahepatic disease. Primary endpoint is OS. Main secondary endpoints are overall disease-free survival (DFS), time-to-progression (TTP), time-to-local-progression (TTLP), primary and assisted technique efficacy (PTE, ATE), procedural morbidity and mortality, length of hospital stay, assessment of pain and quality of life (QoL), cost-effectiveness ratio (ICER) and quality-adjusted life years (QALY).

Pain analysis will be performed using visual analogue scale questionnaires (VAS) assessed prior to, directly after and every 3 months after local treatment; administered pain medication will be registered. Quality of life analysis will be performed using European Organisation for Research and Treatment of Cancer Quality of Life questionnaires (EORTC-QLQ-CR29, EORCT QLQ-C30, EQ-5D) prior to, and every 3 months after local treatment. Patients who complete the quality-of life questionnaires at baseline and at least once during treatment and follow-up will be included in the analysis. The largest decrease in quality of life with respect to baseline will be calculated. The Wilcoxon rank sum test will be used to detect statistical differences between the two treatment arms.

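### Incremental QALYs are taken as an unadjusted arm difference although EQ-5D is collected at baseline: a small, avoidable loss of precision in the ICER

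*Protocol article*

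**What the plan says.** All references are to the protocol article.

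- **QALY construction** (Cost analysis): "QALYS will be calculated by using the utility scores linked to the various health states of the EQ-5D", that is, time weighted by utility. Total QALYs per arm are the main health outcome of the economic evaluation.
- **Estimator** (Cost analysis): "The difference in total costs and total QALYs in both arms will be used to calculate the incremental cost-effectiveness ratio (ICER"), followed by the formula "ICER = (Cintervention - Ccontrol)/(QALYintervention - QALYcontrol").
- **Horizon** (Cost-effectiveness analysis, General considerations): "using a 3-year time horizon".
- **Missing data and uncertainty** (Cost analysis): "Missing data on costs and utilities will be imputed using multiple imputation", and "a probabilistic sensitivity analysis will be performed using the non-parametric bootstrap with 5000 replications".
- **Baseline measurement**: Follow-up states "Quality of life questionnaires will be assessed at baseline, every 3 months for the first year and every 6 months hereafter accordingly". Primary and secondary objectives lists the instruments as "EORTC-QLQ-CR29, EORCT QLQ-C30, EQ-5D) prior to, and every 3 months after local treatment". The two sections differ on the later schedule, but both include a pre-treatment measurement.

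Baseline quality of life is used analytically in one place only: the largest decrease from baseline, compared by Wilcoxon test (Primary and secondary objectives). That analysis does not feed the QALYs.

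**The concern.** A QALY total computed as area under the utility curve starts at the baseline utility, and later utilities correlate with it. If the arms differ by chance in baseline EQ-5D, part of that difference reappears in the QALY difference although treatment did not cause it. It is scaled by the slope of QALYs on baseline utility. The bootstrap is centred on the observed difference, so it shows the resulting uncertainty but does not remove the imbalance.

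At stake is the precision of the ICER denominator. The non-inferiority design expects similar survival in the two arms, so the true QALY difference may be small. The article also links the trial's evidence to reimbursement (Dissemination policy). If adjustment is decided only after the baseline table has been seen, the choice is open to the charge of being result-driven.

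**Working it through.** **1. The plan's own figures.** No precision or power is stated for QALYs or the ICER. The sample size for overall survival reproduces:
- events = 4 × (1.645 + 0.8416)² / (ln 1.3)² = 359.3
- 359.3 / 0.6 = 598.8, so 599
- 599 / 0.97 gives 618, and 618 / 0.90 gives 687

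This point leaves these figures unchanged. They supply 309 patients per arm.

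**2. Inputs from the article.** 309 per arm; 3-year horizon; 36 months of accrual and an event probability of 0.6 about 6.5 years after the last inclusion; EQ-5D at 0, 3, 6, 9, 12, 18, 24, 30 and 36 months (the Follow-up schedule).

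**3. Assumptions, because the article gives no values.** Mean utility 0.80; utility SD 0.15 to 0.25; equal correlation of 0.3 to 0.7 between any two visits of one patient; exponential survival independent of utility; no discounting; no missing data.

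**4. Survival.** Solve 1 − (e^(−6.5λ) − e^(−9.5λ)) / (3λ) = 0.6. This gives λ = 0.115 per year, 3-year survival of about 71%, and mean survival time within 3 years of (1 − e^(−3λ)) / λ = 2.54 years.

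**5. Chance imbalance at baseline.** SE = SD × √(2/309), which is 0.012, 0.016 and 0.020 for SD 0.15, 0.20 and 0.25.

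**6. Effect on QALYs.** Area-under-the-curve QALYs were simulated for 300,000 patients per scenario. With slope b of QALY on baseline utility and correlation r between them:
- 95% chance contribution = 1.96 × b × SD × √(2/309)
- adjusted SE = unadjusted SE × √(1 − r²)

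| SD | Within-patient correlation | b | r | SE unadjusted | SE adjusted | SE reduction | 95% chance contribution (QALY) |
|---|---|---|---|---|---|---|---|
| 0.15 | 0.3 | 0.84 | 0.17 | 0.059 | 0.058 | 1.5% | ±0.020 |
| 0.15 | 0.7 | 1.82 | 0.36 | 0.062 | 0.058 | 6.6% | ±0.043 |
| 0.20 | 0.5 | 1.33 | 0.33 | 0.064 | 0.060 | 5.7% | ±0.042 |
| 0.25 | 0.3 | 0.84 | 0.26 | 0.065 | 0.062 | 3.5% | ±0.033 |
| 0.25 | 0.7 | 1.81 | 0.51 | 0.072 | 0.062 | 13.7% | ±0.072 |

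Central case: 1.96 × 1.33 × 0.20 × √(2/309) = 0.042. The 95% half-width of the QALY difference falls from 1.96 × 0.0641 = 0.126 to 1.96 × 0.0604 = 0.118. In sample-size terms the saving is r², about 11% in the central case and 3% to 25% across the grid.

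**7. Scale.** If the true hazard ratio equalled the margin of 1.3, mean survival time within 3 years would fall from 2.537 to (1 − e^(−3 × 0.1497)) / 0.1497 = 2.417 years. At mean utility 0.80 that is 0.80 × 0.120 = about 0.10 QALY.

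**The case against.** **The formula is a definition.** It defines any ICER and would hold equally with regression-adjusted means, and a health-economic plan that is not shown could add the adjustment. This limits the point: nothing in the section is false or contradictory. But the section goes beyond the definition. It says which difference is used, and it fixes discounting, imputation and the bootstrap, with no baseline term. One can therefore recommend a better estimator without treating silence as an error.

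**This is not bias.** A reader might infer that the ICER is biased or that the bootstrap intervals are invalid. The documents do not support that. Allocation is randomized, the unadjusted difference is unbiased, and a non-parametric bootstrap includes the variance due to baseline imbalance. The planes and acceptability curves would be honest, only slightly wider than necessary.

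**The gain is modest.** Mortality drives much of the variance of 3-year QALYs. A reader might infer a rise in power from 80% to about 90%. That needs a correlation of 0.5 between baseline utility and total QALYs, which only the most favourable corner of the grid reaches. It also borrows the 80% from the overall survival design, since the article plans no QALY test and states no QALY power. A reader might also infer that adjustment would settle the sign of the QALY difference. It would not: in the central case the half-width exceeds the 0.10 QALY benchmark with or without adjustment. These limits stand.

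**Timing of the baseline value.** The questionnaire is specified as before treatment, and low-burden patients are randomized before the procedure (Inclusion; Randomization). A pre-randomization value is therefore not assured for them. This is a matter for the wording of the remedy and does not count against it.

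**Conclusion.** The point holds as a minor improvement in precision. As written, incremental QALYs are an unadjusted difference, while a prognostic baseline covariate is already collected. Adjustment would reduce the standard error of the 3-year QALY difference by about 6% (range 1.5% to 14%). It would also take out a chance component with a 95% range of about ±0.04 QALY (±0.02 to ±0.07). These sizes rest on the assumed utility SD, within-patient correlation and exponential survival; only the horizon, arm size, visit schedule and event probability come from the article. The point concerns one part of a secondary economic endpoint and says nothing against the overall survival comparison.

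**What to change.** In Cost analysis, add that incremental QALYs are estimated by regressing total QALYs on arm and baseline EQ-5D utility (the pre-treatment value, taken before randomization where possible), and that the adjusted arm difference enters the ICER. State that the regression is refitted within each bootstrap replicate and each imputed data set, and that the unadjusted difference is reported as a sensitivity analysis.

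The cost is a sentence or two of analysis text and one regression inside the planned bootstrap. No extra patients, visits or questionnaires are needed, and missing baseline utilities fall under the multiple imputation already planned. The change should be fixed before baseline data are compared by arm.
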